**Table 2 Tab2:**
[figure not shown]
Schedule of enrolment, interventions, and assessments

### Sample size

The sample size calculation for this trial was performed using the PASS 15 [Power Analysis and Sample Size Software (2017). NCSS, LLC. Kaysville, UT, USA]. The primary endpoint of the main study was the surge in %FEV1, a rise from 45% ± 13% to 47% ± 14.5% was seen in the study of Jeong Uk Lim [23], which means a 2% increase in the intervention group. Considering no changes in %FEV1 in the control group, based on a power of 80% and an alpha value of 5% and using the *t*-test for the difference between two means in a 2 × 2 cross-over design, it was calculated that a total sample size of 20 patients (10 in each group) would be sufficient to detect the presumed difference. No drop-out was considered.

### Randomization process

A total of 20 eligible patients will be enrolled in the trial. Central computerized permuted blocked randomization will be performed using a 1:1 allocation schedule with random block sizes of 4. The randomization process is performed by investigators who are not involved in participant recruitment. The allocation sequence will be concealed from the researchers using sequentially numbered, opaque, and sealed envelopes.

### Study drug

Patients will receive inhaled tiotropium bromide (KP-Tiova Rotacaps 18 mcg, Cipla, India) or placebo (KP-Tiova Placebo with lactulose, Cipla, India) which was produced by the same manufacturer. Tiotropium bromide Revolizer or placebo is added to usual standard care and in the treatment period. Standard usual care consists of inhaled corticosteroids and long-acting beta-2 agonists in a fixed combination in the formulation and dosage which were prescribed to the patient before study enrollment. Other immunosuppressive or GVHD modifying agents must be administered through the study at a dose similar to the study onset. All the patients must be instructed regarding the self-administration of study treatment at the onset of the trial. Subjects will be advised to take the study drug at the same time every day according to approved instructions.

### Outcomes

#### Primary outcome

The change from baseline in the measured % FEV1 1 month after treatment with tiotropium bromide Revolizer or placebo added to usual care in stable symptomatic post-HSCT-BOS.

#### Secondary outcomes

The change from baseline in the mean forced expiratory volume in 1 s (FEV1) (mL) 1 month after treatment with tiotropium bromide Revolizer or placebo added to usual care in stable symptomatic post-HSCT-BOS.The changes from baseline in the mean percent predicted FEV1 (%FEV1) (%), and FVC after treatment with tiotropium bromide Revolizer or placebo added to usual care in stable symptomatic post-HSCT-BOSThe change from baseline in the mean NIH Lung Symptom Score after treatment with tiotropium bromide Revolizer or placebo added to usual care in stable symptomatic post-HSCT-BOSThe proportion of complete or partial response rate after treatment with tiotropium bromide Revolizer or placebo added to usual care in stable symptomatic post-HSCT-BOS (in regards to NIH 2014 criteria, a complete response (CR) is defined as normalization of %FEV1 to above 70%. Partial response (PR) is defined as an increase by 10% predicted absolute value of %FEV1)The change from baseline in 6-min walk test distance after treatment with tiotropium bromide Revolizer or placebo added to usual care in stable symptomatic post-HSCT-BOSThe change from baseline in SF-36 score after treatment with tiotropium bromide Revolizer or placebo added to usual care in stable symptomatic post-HSCT-BOSThe change from baseline in SGRQ score after treatment with tiotropium bromide Revolizer or placebo added to usual care in stable symptomatic post-HSCT-BOSThe change from baseline in CQLQ score after treatment with tiotropium bromide Revolizer or placebo added to usual care in stable symptomatic post-HSCT-BOSThe change from baseline in VAS score after treatment with tiotropium bromide Revolizer or placebo added to usual care in stable symptomatic post-HSCT-BOSThe change in admission rates due to respiratory, mediastinal, and thoracic disease after treatment with tiotropium bromide Revolizer or placebo added to usual care in stable symptomatic post-HSCT-BOSThe rate of adverse events rates after treatment with tiotropium bromide Revolizer or placebo added to usual care in stable symptomatic post-HSCT-BOS.

### Adverse events

The adverse events will be examined by open questions, as well as symptoms, and by precise questions about the potentially related adverse effects of the tiotropium which was used in the trial, as xerostomia, pharyngitis, and cardiovascular events like hypertension, edema, and chest pain, etc. The rate of adverse effects will be determined by linking the frequency of adverse events in the experimental drug and placebo by calculating the NARAJNJO scale***.***

### Data entry and management of data files

Data will be entered into a computerized database with the Excel software. All participants’ data and patient health information will be confidential and protected during and after the trial. A code will be used to identify study participants, that will not be given to anybody outside of the study staff except when required by law. Records will be stored in an area with two locked doors. Only the study staff will have access to the locks.

### Monitoring

This is a small investigator-initiated trial, within an academic environment, the responsibility of auditing the trial lies in the hands of the both steering committee and the ethical committee, in which both will have periodical inspections. Details of adverse events will be collected at each study visit. serious adverse events will be reported and assessed by the investigators by means of survival analysis and calculation of hazard ratio.

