**Fig. 1 Fig1:**
[figure not shown]
Study design overview

The crossover design will consist of two sequences with two treatment periods (AB/BA or BA/AB) each lasting 1 month and separated by a 1-week wash-out period. In treatment period A or B, patients will receive tiotropium bromide or a placebo Revolizer added to usual standard care. Patients will be screened for eligibility and, once confirmed, will be randomized (1:1) to each treatment sequence. After completing the first treatment period in the sequence, patients will undergo a 1-week wash-out period in which they receive only the usual standard care. Then, they will receive the alternative treatment period which they have not received yet. Patients allocated to treatment sequence 1 will receive treatment period A, then wash-out period, and then treatment period B; patients randomized to treatment sequence 2 will receive treatment period B, then wash-out period, and then treatment period A.

Patients who are referred to pulmonary clinics will be screened for eligibility criteria. Baseline data must be collected before enrollment. Baseline data include age, gender, time from transplantation, time from diagnosis of BOS, prior and current immunosuppressive and topical respiratory medication history, other medications, NIH lung symptom score, and chronic GVHD activity in other organs. Spirometry and a 6-min walking test (6MWT) must be performed before enrollment. All patients are required to complete a 36-Item Short Form Survey (SF-36), Cough Quality-of-Life Questionnaire (CQLQ), and St. George’s Respiratory Questionnaire (SGRQ) before enrollment.

A total of 20 eligible patients will be enrolled in the trial. Central computerized permuted blocked randomization will be performed using a 1:1 allocation schedule with random block sizes of 4. The randomization process is performed by investigators who are neither involved in participant recruitment, nor study conduct and assessment evaluation. The allocation sequence will be concealed from the researchers using sequentially numbered, opaque, and sealed envelopes.

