During the treatment period A, patients will receive inhaled tiotropium bromide (KP-Tiova) at a dose of 18 mcg once daily in the morning plus usual standard care. Standard usual care consists of inhaled corticosteroids and long-acting beta-2 agonists in a fixed combination in the formulation and dosage which were prescribed to the patient before study enrollment. Other immunosuppressive or GVHD modifying agents must be administered through the study at a dose similar to the study onset. All the patients must be instructed regarding the self-administration of study treatment at the onset of the trial.

During the treatment period B, patients will receive a tiotropium bromide placebo Revolizer plus standard usual care. The placebo Revolizer is identical to the experimental Revolizer in appearance, smell, taste, and texture and is administered on the same schedule as the experimental treatment.

In the wash-out period, patients receive only standard usual care as above. The wash-out period is supposed to last 1 week.

Patients will continue to receive study schedules until completion of the trial, occurrence of unacceptable adverse events, progressive pulmonary disease, change in immunosuppressive agents due to alterations in GVHD activity in other organs, malignancy relapse or graft failure, and withdrawal of consent.

Assessments will be performed at the end of the first treatment period, at the end of the wash-out period, and at the end of the second treatment period. Assessments include spirometry, 6MWT, NIH lung symptom score, GVHD activity in other organs, SF-36 score, SGRQ score, CQLQ score, VAS score, and monitoring of adverse events.

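### The hazard ratio for serious adverse events has no defined contrast and will rest on very few events, and the Naranjo scale cannot supply the adverse-event rate listed as a secondary outcome

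*Protocol article*

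**What the plan says.** Serious events are covered in the protocol article under Monitoring: "serious adverse events will be reported and assessed by the investigators by means of survival analysis and calculation of hazard ratio". The section names no comparison, time origin or treatment of repeated periods. It adds that "Details of adverse events will be collected at each study visit".

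Adverse events in general have their own section: "The rate of adverse effects will be determined by linking the frequency of adverse events in the experimental drug and placebo by calculating the" Naranjo scale (spelled differently in the article). The rate of adverse events after tiotropium or placebo is the last item under Secondary outcomes.

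The Study design section sets two treatment periods, "each lasting 1 month and separated by a 1-week wash-out period". After the first, patients have the wash-out; "Then, they will receive the alternative treatment period which they have not received yet". Not everyone need get that far: "Patients will continue to receive study schedules until completion of the trial, occurrence of unacceptable adverse events", among other reasons for stopping.

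Statistical methods gives a paired t-test for treatment and t statistics for period, interaction and sequence. It names no method for event counts and excludes adjusted analyses because the sample is small.

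**The concern.** There are two separate faults: one concerns serious events, the other adverse events in general.

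For serious events, an ordinary two-group hazard ratio does not fit this design. If the groups are the randomised sequences, both groups receive both treatments and the contrast largely cancels. If the groups are the treatments, the same patients appear on both sides and the usual standard error treats their two records as independent. Patients stopped by harm in period 1 also contribute nothing to the other treatment. Whichever contrast is meant, 20 patients give at most 20 × 1 = 20 patient-months per treatment, so few serious events can be expected.

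For adverse events, the Naranjo scale scores how likely it is that a drug caused one event in one patient. Calculating it gives neither a rate nor a difference between treatments, so the stated rule does not lead to the listed secondary outcome.

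At stake is the safety statement. A hazard ratio of zero, infinity or with a very wide interval could be read as evidence of safety or of harm when it is neither.

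**Working it through.** **Inputs from the article.** 20 patients, 10 per sequence; two 1-month periods; 1-week wash-out. It gives no serious-event risk, hazard ratio or event count, so there is no safety figure to reproduce.

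**Assumptions.** Serious-event risk p per patient-period of 2%, 5%, 10% and, for the upper end, 20%; a true hazard ratio of 2 where an effect is needed.

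**1. Chance that at least one treatment has no serious event.** This takes 20 patients on each treatment, the same risk p on both, and independence between treatments: 1 − (1 − (1 − p)^20)^2.
- p = 2%: 0.98^20 = 0.668; 1 − 0.332^2 = 0.89
- p = 5%: 0.95^20 = 0.358; 1 − 0.642^2 = 0.59
- p = 10%: 0.90^20 = 0.122; 1 − 0.878^2 = 0.23

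In those cases the hazard ratio is zero, infinite or undefined.

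**2. Precision when it can be estimated.** With 4 events split 2 and 2, the approximate 95% interval for independent groups runs by a factor exp(1.96 × √(1/2 + 1/2)) = 7.1 in each direction.

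**3. Events needed against events expected.** For a hazard ratio of 2, 80% power and two-sided 5%, Schoenfeld's formula gives 4 × (1.96 + 0.84)^2 / (ln 2)^2, about 66 events; Freedman's gives 71. Expected events are 20 × [p + 1 − (1 − p)^2], where p is now the placebo risk:

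| Placebo risk per month | Expected events | Approximate power |
|---|---|---|
| 2% | 1.2 | 6% |
| 5% | 3.0 | 9% |
| 10% | 5.8 | 13% |
| 20% | 11.2 | 21% |

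**4. What the choice of contrast does.** Simulated 2 × 2 crossover, 6,000 patients, placebo risk 20% per month, true within-patient hazard ratio 2, gamma frailty with variance 0, 1 or 3, no drop-out:

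| Contrast | Variance 0 | 1 | 3 |
|---|---|---|---|
| By sequence, first event | 1.08 | 1.07 | 1.10 |
| By treatment, unpaired | 2.01 | 1.91 | 1.64 |
| First period only | 1.96 | 1.89 | 1.75 |
| Stratified by patient | 2.04 | 2.10 | 1.90 |

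The sequence contrast nearly loses the effect. The unpaired ratio falls as patients differ more in risk. The first-period ratio, which has no pairing to ignore, falls too, so that attenuation reflects unmodelled heterogeneity. What ignoring the pairing affects is the standard error, which was not quantified here. The patient-stratified ratio stays near 2.

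**5. What an exact paired test can show.** With k discordant patients all in one direction, the two-sided p-value is 2 × 0.5^k: 0.0625 for k = 5 and 0.031 for k = 6. At least 6 are needed for p < 0.05.

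**6. The Naranjo clause.** No arithmetic applies. Secondary outcomes calls for a rate after each treatment; the Adverse events section obtains it by "linking the frequency of adverse events in the experimental drug and placebo by calculating the NARAJNJO scale". The frequencies are the right raw material, but the score attached to them is a per-event judgement.

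**The case against.** A reader might infer that a crossover rules out any hazard ratio. The article does not support that: it says only that one will be calculated, and step 4 shows that a patient-stratified or first-period ratio recovers the effect reasonably well. The contrast might also be defined in a full protocol or analysis plan not shown here. This stands, and it limits the first fault to an undefined contrast and too few events. It does not rescue the method: a stratified ratio uses only within-patient contrasts and a first-period ratio discards half the exposure, so both make the sparsity worse.

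A reader might also infer that the zero-event figures demonstrate a pairing error. They do not. They measure rarity, assume independence between treatments, and would affect any ratio. At 10% risk both treatments have events 77% of the time.

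Nor does the article lack any comparison of adverse events. It plans frequencies on drug and on placebo; only the scale is the wrong tool for relating them. The article does not describe the scale, so this part rests on general knowledge of the instrument.

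Finally, a paired exact test is no full replacement. It drops patients who stop in period 1, who may matter most for safety, and it is weak. That stands and shapes the fix.

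**Conclusion.** Both faults hold in limited form. The hazard ratio for serious events is stated without a contrast or within-patient handling, in a trial where the sequence contrast would give about 1.1 for a true value of 2. An expected 1 to 11 events compare with the 66 or so needed to detect that value. The Naranjo scale does not deliver the adverse-event rate listed as a secondary outcome, although the frequencies that could deliver it are planned.

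The event risks, the hazard ratio of 2 and the frailty variances are assumptions, since the article gives none. The conclusion that events will be few holds across the range shown. The Naranjo point depends on none of these figures.

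The primary efficacy analysis is unaffected. The change is still worth making, because it concerns a listed outcome and the reporting of serious harm.

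**What to change.** - **Monitoring:** delete the survival analysis and hazard ratio. List every serious event by treatment at onset, period and sequence, with a stated rule for attributing events that begin in the wash-out.
- **Adverse events:** report the number and proportion of patients with at least one event, and events per patient-time, by treatment and period. Include all patients exposed to that treatment, also those who stop in period 1.
- **Supportive only:** an exact paired (McNemar-type) comparison among patients with both periods.
- **Naranjo score:** keep it solely as a causality description for each event.

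The cost is wording in two sections; the data are the same, provided that onset dates are recorded. There is a small downside. The paired comparison leaves out patients who do not cross over and has very little power, so safety reporting will be mainly descriptive, and the article should say so.

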### Ethics approval and dissemination

Participants will be asked to sign the approved informed consent form before participating in the study. The study protocol (protocol version 1.0, issue date: Dec 2021) was approved by the Ethics Committee of the Imam Khomeini Hospital Complex, Tehran University of Medical Science under the number IR.TUMS.IKHC.REC.1400.361. The trial is conducted in keeping with Good Clinical Practice Guidelines, the ethics drawn in the Declaration of Helsinki, and applicable local laws and regulations. The trial is registered at www.irct.ir under the identification number IRCT20200415047080N3. Informed consent will be signed. Clinical results will be available in a medical journal and presented at national or international conferences. De-identified data can be supplied upon request with data usage agreements to ensure scientific dissemination and transparency. There is no anticipated harm and compensation for trial participation.

### Statistical methods

The analysis will be done by intention-to-treat and per-protocol. Assessment for various effects in the cross-over design will be performed via the following statistical methods:Treatment effect (comparison between the intervention and control) will be investigated by paired *t*-test.Period effect (the effect of the same treatment received at two different periods is different for each period) will be assessed by the *t* statistics, as follows:$$t=\frac{ {dY}_{\mathrm{diff }\ \left(T-P\right)}- {dY}_{{\mathrm{diff}}\ \left(P-T\right)}}{\sqrt{^{{{\text{SD}}}_{\left(T-P\right)}^{2}}\!\left/ \!_{ {n}_{(T-P)}}\right.+^{ {{\text{SD}}}_{\left(P-T\right)}^{2}}\!\left/ \!_{ {n}_{(P-T)}}\right.}}$$where *dY*_diff(*T*–*P*)_ is the mean difference in changes of “endpoint Y” in treatment sequence followed by placebo, SD^2^_(*T*–*P*)_ was the variance of the difference of “endpoint Y” and *n*_(*T*–*P*)_ was the number of patients in this sequence. Definitions for the *P*–*T* sequence are the same.Period-by-treatment interaction (whether the two treatment effects are different in the two periods), will be evaluated by the t statistic as follows:$$t=\frac{ {\mathrm{total}\ \mathrm{Mean}\ dY}_{ \left(T-P\right)}- {\mathrm{total}\ \mathrm{Mean}\ dY}_{ \left(P-T\right)}}{\sqrt{^{{{\text{SD}}}_{\mathrm{total}\ \mathrm{Mean}\ \left(T-P\right)}^{2}}\!\left/ \!_{ {n}_{(T-P)}}\right.+^{ {{\text{SD}}}_{\mathrm{total}\ \mathrm{Mean}\ \left(P-T\right)}^{2}}\!\left/ \!_{ {n}_{(P-T)}}\right.}}$$In which:$${\mathrm{total}\ \mathrm{Mean}\ dY }_{(T-P)}= \frac{\sum_{1}^{n}{\mathrm{individual\ Mean}\ dY}_{(T-P)}}{{n}_{(T-P)}}$$And:$${\mathrm{individual\ Mean}\ dY}_{(T-P)}=\frac{{dY}_{\mathrm{ after\ Treatment\ in}\ \left(T-P\right)}+{dY}_{ \mathrm{after\ Placebo\ in}\ \left(T-P\right)}}{2}$$It may be considered as the carry-over effect.Sequence effect (comparison between the results in AB and BA sequences) will be performed by independent sample *t*-test [26].

As a result of a small sample, no further additional analyses (e.g., subgroup and adjusted analyses) will be done.

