### Eligible participants

The outpatient BOS cases of the pulmonology clinic of Shariati Hospital and Taleghani Hospital were selected. Patients to be enrolled are required to meet all inclusion criteria listed in Table 1 and not meet any of the exclusion criteria. Those with BOS patients with baseline 20% ≤ %FEV1 < 70% will be selected and contacted by telephone. The eligible participants will be asked to visit the research center.

**Table 1 Tab1:** Inclusion and exclusion criteria

Exclusion criteria	Inclusion criteria
1) Life expectancy < 6 months at the time of enrollment as judged by the enrolling investigator	1) Subjects able to sign the Informed Consent
2) The need for chronic oxygen therapy	2) 18 years of age or older
3) Baseline %FEV1 ≤ 20%	3) Diagnosis of post-HSCT-BOS according to NIH 2014 criteria
4) History of thoracic air leak syndrome	4) Baseline %FEV1 < 70%
5) Documented respiratory infection	5) Must be symptomatic, defined as NIH Lung Score 1–3, and no other contributing etiology (including cardiac diseases, infection, anemia, or extrinsic thoracic compression) is present for respiratory symptoms
6) Active malignancy	6) Stable disease defined as less than 10% change in %FEV1 during the past 3 months while having no change in immunosuppressive and topical respiratory medications in the past 3 months
7) Graft failure	7) Must have received a combination of inhaled corticosteroid and inhaled long-acting beta-2 agonist during the past 3 months
8) Known history of asthma or chronic obstructive lung disease (COPD)	8) No new or supplemental immunosuppressive therapy for extra-thoracic GVHD during the past 3 months
9) Active smoking during the past 12 months	9) Patients with prior exposure to short-acting or long-acting inhaled anti-cholinergic drugs are eligible unless they have been received within the past 3 months
10) Substance abuse or uncontrolled psychiatric disorder	10) Ability to use Revolizer
11) Pregnant or nursing women	
12) Daily corticosteroid of more than 1 mg/kg prednisone equivalent	
13) Known intolerance or allergy to anticholinergic drugs	
14) History of urinary retention, angle-closure glaucoma, CrCl ≤ 30 ml/min	
15) History of arrhythmia in past years, MI in past 6 months, or hospital admission due to heart failure in past year	
16) Ongoing participation in any other clinical trial (more typical would be using an investigational agent within 28 days of enrollment)	

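### The treatment comparison is a paired t-test not limited to continuous outcomes, and no other test is given for the yes/no response outcome, where it can be undefined

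*Protocol article*

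**What the plan says.** The methods list in the article's Statistical methods section opens: "Assessment for various effects in the cross-over design will be performed via the following statistical methods". Its first item is the treatment comparison: "Treatment effect (comparison between the intervention and control) will be investigated by paired" t-test. The formula for the period effect is written for a generic endpoint Y, and nothing ties the list to %FEV1. The section ends by saying that, because the sample is small, "no further additional analyses (e.g., subgroup and adjusted analyses) will be done".

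Secondary outcomes include the proportion with a complete or partial response. The definitions are "a complete response (CR) is defined as normalization of %FEV1 to above 70" per cent, and "Partial response (PR) is defined as an increase by 10% predicted absolute value of %FEV1". Each patient is therefore a responder or a non-responder in each period. The same list has an outcome on hospital admissions. Neither outcome has a method of its own. Serious adverse events do: the Monitoring section gives them survival analysis and a hazard ratio.

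**The concern.** The within-patient difference in a yes/no outcome can only be -1, 0 or +1. If all 20 differences are 0, their SD is 0, the t statistic is 0/0 and a t interval shrinks to one point, as if 20 patients had shown exact equality. If a few patients differ, all in one direction, the t p-value can be well below the exact one.

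The plan's thresholds make sparse tables plausible. Response needs a 10-point rise or a value above 70%, while the Sample size section expects a mean rise of 2 points on tiotropium and none on placebo. At stake is whether the response comparison gives a usable result, and whether a nominally significant one could depend on an unsuitable test.

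**Working it through.** **Inputs from the article.** 20 patients, hence 20 pairs; 80% power; 5% alpha, taken as two-sided (Sample size). "a rise from 45% ± 13% to 47% ± 14.5% was seen", "which means a 2% increase in the intervention group", and no change in controls (Sample size). Eligibility: "baseline 20% ≤ %FEV1 < 70" per cent (Eligible participants). Response thresholds as above (Secondary outcomes). No SD of change or of within-patient differences, no response rate and no admission rate are given.

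**1. The plan's sample size.** In a 2 × 2 crossover t-test, the SE of the treatment difference is SD_diff/√20, with 18 degrees of freedom. Solving for 80% power at a 2-point difference gives SD_diff ≈ 3.02. The printed SDs do not give 20: used as SD_diff, 13 needs 334 patients and 14.5 needs 416. So 20 cannot be reproduced from what is printed, and 3.02 is a back-solved assumption.

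**2. How often the test is undefined.** Model: baseline normal (45, SD 13) cut to 20–70; independent normal changes with mean +2 on tiotropium and 0 on placebo; response if the change is at least 10 points or the value passes 70. Let b and c be the probabilities of responding on tiotropium only and on placebo only. Then P(no discordant pair) = (1 − b − c)^20.

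| SD of each period's change | b + c | P(no discordant pair) |
|---|---|---|
| 3.02 | 0.0177 + 0.0047 = 0.0224 | 0.9776^20 ≈ 64% |
| 4 | 0.0371 + 0.0122 = 0.0493 | 0.9507^20 ≈ 36% (37% in a separate run) |
| 5 | 0.0672 + 0.0288 = 0.0960 | 0.9040^20 ≈ 13% |
| 7 | 0.1274 + 0.0739 = 0.2013 | 0.7987^20 ≈ 1% |

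At 3.02, a further 29% of trials have exactly one discordant pair, so 93% have at most one. The first row uses 3.02 as the SD of each change. If it is instead the SD of the difference between two independent changes, each change has SD 3.02/√2 = 2.14 and the undefined share is 75%.

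**3. What the t-test returns with 20 pairs.** This step needs no model. For a split of k patients to 0, the mean difference is m = k/20, the variance is (k − 20m²)/19, and SE = √(variance/20). The critical t on 19 degrees of freedom is 2.093.

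- 0-0: SE = 0, t = 0/0, interval 0 to 0. The Tango score interval is ±z²/(n + z²) = ±3.84/23.84 = ±16.1 points.
- 1-0: m = 0.05, SE = 0.050, interval -5.5 to +15.5 points. Score: -11.9 to +23.6.
- 2-0: interval -4.4 to +24.4. Score: -7.7 to +30.1.
- 4-0: m = 0.20, SE = 0.0918, t = 2.18, p = 0.042, interval 0.8 to 39.2. Score: 0.7 to 41.6. Exact McNemar: 2 × (1/2)^4 = 0.125. Mid-p: 0.125 − 0.0625 = 0.0625.

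**4. Type I error.** Enumerating all tables under the null, for discordance from 1% to 90%, the t-test rejects at most about 5.7% of the time; from 1% to 25%, at most 4.8%.

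**The case against.** The strongest reply is that the article never says in words that the t-test will be used for response. Its formulas are in changes, response is worded as a proportion, and a test for one secondary outcome is the kind of detail that an article leaves to the full protocol or analysis plan. The first part is right: the application is inferred. But the point concerns a stated method with no limit on its scope, not a missing detail, and the article names a separate method where it wants one, as for serious adverse events.

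Several other replies stand:

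- A reader might take the closing sentence to bar any other test. Its examples are subgroup and adjusted analyses, so it does not forbid a suitable test for a listed outcome.
- A reader might extend the result to admissions. No admission rate is stated, so the plan's figures show nothing there.
- The section specifies tests and promises no interval, so the interval comparison matters only if one is reported.
- A reader might conclude that t intervals are far too narrow in general. That holds at 0 or 1 discordant pairs; by 4-0 the t and score intervals nearly agree.
- The 4-0 split is rare where the test is most often undefined: under 0.1% of trials at SD 3.02.
- With no discordant pair exact McNemar gives p = 1, which says little either. But it is defined, and the score interval shows how little is known.

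**Conclusion.** The point holds for complete or partial response, as a matter of wording that leaves an unsuitable test in place. With 20 pairs the paired t-test has no value when no patient's response differs between treatments. How often that happens depends on an SD that the plan does not state: about two thirds of trials at an SD of change near 3, about 37% at 4, 13% at 5 and 1% at 7, given normal and independent changes. It is therefore a likely result only if the variability is as small as the sample size needs.

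The single-table results are firm: a t interval, if given, is too narrow at 0 or 1 discordant pairs, and at 4-0 the t p-value falls below 0.05 while exact and mid-p McNemar do not. The documents do not support a claim of inflated type I error, nor of any harm to the primary analysis: %FEV1 is continuous, and a paired t-test suits that type of data. The matter is confined to secondary outcomes.

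**What to change.** In Statistical methods, limit the paired t-test to continuous outcomes. For complete or partial response, report the four-cell paired table (responder on tiotropium only, on placebo only, on both, on neither) and test it with mid-p or exact McNemar, choosing one in advance; use Mainland-Gart by sequence if the period effect is to be removed. If an interval is reported, use a score (Tango) interval for the paired difference. The same approach can serve for at least one admission in a period, though no size of problem can be claimed there.

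This takes one or two sentences and no new data. The cost is a slightly more conservative p-value, less so with mid-p, and wider intervals in sparse tables.
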